## Abstract

**Background:**

Research indicates that many autistic adults are insufficiently active and overly sedentary. There is limited evidence on effective strategies to increase physical activity (PA) and reduce sedentary behavior (SB) in this population. Gamified mobile health (mHealth) interventions show promise for addressing these challenges by leveraging autistic individuals’ strengths in visuospatial learning and their affinity for digital gaming. Despite this potential, it remains unclear how well these interventions translate to real-world settings. This gap is compounded by the lack of community-based participatory approaches in the development of mHealth intervention for autistic adults.

**Objective:**

This study aims to (1) formulate gamification and behavior change strategies for the PuzzleWalk v2 app using a community-based participatory approach and (2) evaluate its feasibility and acceptability for increasing PA and reducing SB among autistic adults, including those with mild intellectual disability, in real-world settings.

**Methods:**

This study, consisting of 2 sequential phases, will be conducted entirely remotely: (1) online community-based design workshops to refine the PuzzleWalk gamified mHealth system with input from key autism stakeholders, including autistic adults and caregivers, and (2) an 8-week field deployment to assess real-world usability and engagement. In Phase I (completed), weekly workshops and usability testing focused on understanding autistic adults’ technology preferences, evaluating PuzzleWalk v1 and v2 prototypes, and incorporating stakeholder feedback into iterative app development (n=9). Phase II (in progress) will involve a single-arm clinical trial where approximately 70 participants will use the app alongside research-grade activity-tracking accelerometers to measure PA and SB. Outcome measures, including sedentary time, step counts, PA intensities, and app engagement (eg, time spent using the app), will be collected across 4 specific time points (ie, baseline and weeks 3, 5, and 8). Repeated measures ANCOVA will be performed to examine changes in participants’ objective levels of PA and sedentary time before, during, and after the intervention.

**Results:**

Phase I of the study, involving community-based participatory design workshops and usability testing, was completed in November 2024. Key autism stakeholders recognized the gamified PuzzleWalk app as a viable tool for enhancing motivation toward PA and SB changes among autistic adults. Data collection for Phase II, the field deployment, is currently underway and is expected to end in August 2025. As of July 2025, we had enrolled 69 participants in the study. The findings of these studies will be shared in a subsequent peer-reviewed publication.

**Conclusions:**

Results of the ongoing field deployment study (Phase II) will further clarify the app’s effectiveness and real-world applicability.

**Trial Registration:**

ClinicalTrials.gov NCT06566131; https://clinicaltrials.gov/study/NCT06566131

**International Registered Report Identifier (IRRID):**

DERR1-10.2196/71631

## Introduction

### Background

Increased awareness and advancements in diagnostic methods have made autism spectrum disorder (ASD) one of the most rapidly growing developmental disabilities in the United States [1,2]. However, poor health outcomes among autistic adults have emerged as a significant public health concern. Approximately 5.4 million American adults were diagnosed with this lifelong neurodevelopmental condition, with or without co-occurring intellectual disability [3]. Autistic adults are at higher odds of lifestyle-related chronic health conditions, including obesity (1.4-fold), dyslipidemia (2.1-fold), and diabetes (2.2-fold) [4,5].

The *Healthy People 2030* initiative highlights the importance of regular physical activity (PA) participation for maintaining overall health among individuals with and without disabilities. However, more than one-quarter of American adults, including autistic adults, participate in no leisure-time PA [6]. Research findings indicate that individuals with ASD often exhibit lower PA levels and increased sedentary behavior (SB) with age, potentially due to diminished intrinsic motivation to move and heightened sensory sensitivities in public environments [7,8]. Moreover, evidence [9] categorizes SB as a distinct health risk factor, as prolonged sitting contributes to adverse health outcomes even among those meeting PA guidelines (ie, accumulating ≥150 minutes a week of moderate-to-vigorous PA [MVPA] or ≥75 minutes a week of vigorous aerobic PA) [10]. Physical inactivity and excessive sitting may contribute to the high prevalence of chronic health conditions in autistic adults [4]. Despite these concerns, strategies to enhance preventive health behaviors in autistic adults remain under-researched. Studies investigating PA and SB in autistic adults frequently show methodological limitations, such as small sample sizes and the underrepresentation of individuals with co-occurring intellectual disability [11].

Gamified mobile apps hold promise for effectively promoting positive changes in PA and SB in autistic adults by leveraging their unique strengths in visuospatial learning and digital gaming [12-15]. It is well documented that technology particularly appeals to autistic adults because it provides a structured, consistent experience with lower social demands than face-to-face communication [13,16]. Gamified behavioral interventions delivered via smartphone apps have rapidly expanded the potential for improving health behaviors in a way that is engaging and cost-effective. The gamification approach can enhance a user’s perception of autonomy, fostering intrinsic motivation and contributing to enjoyable experiences, which collectively sustain their engagement [17]. However, most evidence on the efficacy of gamification approaches in promoting free-living PA comes from studies involving typically developing young people, with a lack of rigorously designed empirical studies involving autistic populations [18]. Financial incentive–based apps have also emerged as a viable strategy for increasing PA and reducing sedentary time, particularly for individuals with low motivation for voluntary behavior change [19]. Although preliminary evidence suggests that such apps can improve PA and reduce SB in both autistic and nonautistic groups, questions remain about the long-term sustainability of these interventions. Early versions of gamified mobile health (mHealth) apps, such as PuzzleWalk v1, laid a significant foundation as innovative, strength-based interventions for autistic adults, but they did not yield long-term improvements in PA and SB changes in a small sample of autistic adults [20]. Existing mHealth interventions aimed at promoting PA often encounter pragmatic barriers, including difficulty of use, limited system integration, poor scalability, and lack of personalization, which can lead to reduced user engagement and adherence [21-23]. These challenges may be more pronounced for autistic adults who often face additional barriers related to sensory sensitivities and the need for structured routines and consistent feedback [4,7,8]. Furthermore, few efforts have been made to integrate community input during the design and development of mHealth apps [18]. This gap directly informed this study, which centers on the co-design of PuzzleWalk v2 to enhance both real-world usability and sustained engagement for autistic adults.

While most studies on PA have disproportionally focused on young adults (eg, 18-30 years old) without co-occurring intellectual disability, a substantial proportion of young autistic adults remains insufficiently active [11,24]. Current evidence on interventions designed to promote PA and reduce SB in autistic adults remains limited and is frequently characterized by poor methodological rigor in the development and evaluation of intervention strategies [11]. Gamified mHealth interventions represent a promising approach for facilitating positive PA and SB changes by leveraging the distinct strengths and preferences of autistic individuals. Addressing adoption challenges and evaluating the real-world applicability of gamified mHealth interventions are essential for improving preventive health behaviors within this community.

### Study Aims

This paper presents a study protocol for the remote co-design and field-testing of a novel mHealth system, guided by gamification and behavior change theories. The overarching objective of this study is to develop an effective and sustainable mHealth intervention that promotes regular PA participation and reduces SB in autistic adults using a community-based participatory research approach. The study’s specific aims are to (1) develop practical gamification strategies that promote PA and SB changes in autistic adults and (2) evaluate the feasibility and acceptability of the PuzzleWalk v2 mobile app in increasing free-living PA and reducing SB among autistic adults. Developed by the corresponding author’s research team, PuzzleWalk v1 demonstrated the potential to induce short-term behavioral changes in a previous feasibility deployment study [20]. Building on these preliminary findings, this study will refine evidence-based design principles to promote sustained improvements in PA and SB in autistic adults, including those with and without mild intellectual disability.

## Methods

### Study Design

This study comprises 2 sequential phases: (1) online community-based participatory design workshops with autism community stakeholders (Phase I; completed) and (2) an 8-week field deployment of the PuzzleWalk v2 mHealth system in real-world settings (Phase II; in progress).

#### Phase I: Community-Based Participatory Design Workshop

The first phase involved weekly online design workshops with key community stakeholders, including 7 autistic adults, 1 parent or caregiver, and 1 speech therapist with over 15 years of experience working with individuals with ASD. These remote workshop sessions utilized individual interviews and online surveys to evaluate preferences and technology usage patterns, identify applicable gamification and behavior change strategies to enhance engagement and adherence, and review the app’s previous (v1) and current (v2) functional prototypes. Specifically, the workshop sessions focused on (1) exploring technology-related factors that influence PA participation and prevalent SBs in autistic adults, (2) discussing the current features of PuzzleWalk v1 (eg, strengths, weaknesses, and opportunities for improvement), and (3) identifying best-practice intervention strategies to address challenges associated with autism symptoms and enhance user adherence during field deployment (Table 1). Meeting formats were adapted to accommodate the diverse needs and preferences of stakeholders based on the Academic Autistic Spectrum Partnership in Research and Education (AASPIRE) guidelines [25]. Data from interviews and surveys were analyzed using frequency and narrative data analysis methods. The core findings were shared with the software development team and iteratively incorporated into the PuzzleWalk v2 system. The multiformat co-design workshop guide provides the core questions and discussion prompts used throughout the participatory design phase (see Multimedia Appendix 1). Finally, pilot usability testing was executed with various iPhone models to ensure the app’s technical compatibility and functionality before field deployment.

**Table 1 table1:** Focused activities in community-based participatory design workshops.

Timeline	Activities	Format
Week 1	Screening interviews and general inquiry on demographics, patterns of PA^a^ and SB^b^, and overall health among key stakeholders with ASD^c^	Phone call or virtual meeting
Week 2	Exploration of preferences and patterns of general technology use and its influence on PA and SB among autistic adults	Survey or email
Weeks 3-4	Identification of factors influencing PA participation and perceived health benefits of PA	Survey or email
Weeks 5-6	Evaluation of the core features (eg, step-to-game conversion) and identification of areas for improvement in PuzzleWalk v1	Virtual meeting
3-month period	Integration of key findings into PuzzleWalk v2	Not applicable
Weeks 7-8	Autism-friendly intervention design and pilot compatibility and functionality testing of PuzzleWalk v2 in real-world settings^d^	Survey or email

^a^PA: physical activity.

^b^SB: sedentary behavior.

^c^ASD: autism spectrum disorder.

^d^5 stakeholders who own an iPhone participated in this activity.

#### Phase II: Field Deployment of PuzzleWalk v2 mHealth System

Autistic adults who consent to participate in this single-arm clinical trial (NCT06566131) will receive study materials via the United States Postal Service, including a research-grade accelerometer/monitor (ie, ActiGraph CentrePoint Insight wristwatch), a cable charger, and study instruction sheets. Participants will also receive visual guidelines for wearing the monitor and returning study materials. The monitor wear guide will instruct the participants to wear the monitor comfortably on their nondominant wrist during waking hours, removing it only for water-related activities such as showering or swimming. Each night before bed, participants will record their monitor wear time in their tracking log and remove the watch during sleep. Reminders will be sent to participants every 3 weeks to 4 weeks to ensure uninterrupted use per the manufacturer’s recommendation for the monitor’s charging. The return guide will instruct participants to return the study materials by placing the monitor, charger, and tracking logs in a provided Ziplock bag, sealing them in a prepaid Priority Mailbox, and mailing them back to the research team via United States Postal Service (see Multimedia Appendix 2). Upon receipt, the research team will confirm the return by text message or email.

Before baseline data collection, we will provide a ramp-up familiarization period to help participants understand the study protocol and requirements, and to ensure they are comfortable wearing the activity-tracking accelerometer on their nondominant wrist. Throughout the deployment period, the research team will use SimpleTexting to communicate regularly with study participants and to promptly respond to any questions they have. SimpleTexting is an SMS text messaging service provider that allows the research team to send mass text messages and engage in real-time conversations with participants. Field data collection will begin once the participant completes a demographic survey and confirms receipt of the study package. This includes gathering data on PA and sedentary time using ActiGraph CentrePoint Insight watches and app engagement (eg, time spent using the app and number of session logins) using Voyager, an open-source Laravel administration package (The Control Group). The Voyager database management system will enable the research team to monitor user engagement and manage user profiles in near real time. Specifically, this administration system will be used to identify participants’ mobile devices and update their unique usernames on the leaderboard of PuzzleWalk v2. Starting week 3, participants will begin using PuzzleWalk v2, following a visual, step-by-step user guide, and continue using the app until the end of week 8 (total 6-week intervention). Outcome measures will be collected during 4 time periods: week 1 (baseline), week 3 (intervention start), week 5 (midintervention), and week 8 (intervention end). Periodic reminders and reinforcement messages, incorporating evidence-based behavior change techniques, will support their continued engagement with the app and PA participation (Figure 1).

**Figure 1 figure1:**
[figure not shown]
Data collection flowchart in Phase II. PA: physical activity; SB: sedentary behavior.

### Sample and Recruitment Strategies

This pilot study acknowledges the potential for selection bias because individuals who volunteer for this PA-related study may already have a relatively high level of motivation to change their behavior. According to a priori power analysis using G*Power 3.1 [26], considering an α level of .05, an estimated effect size (f) of 0.2, an anticipated correlation of 0.4 among repeated measures, and 4 measurement levels of within-subjects factors, we project a total sample of 55 autistic adults to achieve a power of 0.9. To be eligible, prospective participants must (1) be adults aged 18 years to 55 years, (2) have received a formal diagnosis of ASD from a qualified medical professional, and (3) own and regularly use a compatible iPhone (iOS 14+ operating system). Android version development is underway, and its users will be invited to participate in future clinical trials. Individuals with moderate-to-profound intellectual disability or orthopedic conditions that significantly interfere with independent information processing or ambulation (eg, using a wheelchair or crutches) will be excluded from the study. These individuals may encounter challenges in engaging with the cognitive and physical aspects of the intervention, such as understanding verbal or written instructions, independently using the app, or meeting study requirements (eg, returning study materials to the research team). Therefore, only individuals who live semi-independently or independently, have autonomy for daily living, and are capable of making their own research-related decisions will be given an informed consent form to sign and subsequently invited to participate in the study. Future research shall explore adaptation strategies to make the mHealth interventions more accessible to a broader autistic population, including those with co-occurring moderate-to-profound intellectual disability.

All participants will provide written or digital consent before participating in study activities. The research team established a multisource recruitment model that leverages national and regional autism advocacy organizations (eg, Autism Speaks, Autism Delaware), Simons Foundation Powering Autism Research for Knowledge (SPARK) research match services, ResearchMatch.org, and online autism support groups on social media (eg, Reddit and Facebook). The study flyer will be posted on the Autism Speaks research search portal (*approval pending*), ResearchMatch.org (*approved*), and relevant group pages on social media channels (eg, Autism Delaware Facebook page; *approved*). Individuals interested in participating in the study can contact the research team directly and undergo a screening interview to verify their eligibility. SPARK’s research match service (*approved*) will identify potential participants based on study criteria and send them study invitations. Our research team will be provided with the diagnostic and contact information of those who consent. Individuals recruited through other channels will undergo a screening interview to confirm their eligibility. The interview will explore details about when and how the ASD diagnosis was made, as well as common autism symptoms. Based on the results from preliminary studies [20,27,28], we expect to recruit all eligible participants within the first 3 months of the study using this multisource recruitment model.

### Ethical Considerations

The study was reviewed and approved by the University of Delaware Institutional Review Board (IRB #2098388), with all procedures adhering to institutional and national ethical standards for research involving human participants. In Phase I, which has been completed, all participants provided written or digital informed consent before engaging in remote community-based design workshops and usability testing. Only individuals with sufficient cognitive and communicative capacity to provide autonomous consent were enrolled. Data collected during this phase were de-identified prior to analysis, and any identifiable information, such as email addresses, was promptly destroyed following data collection. Participant privacy was protected using encrypted communication protocols and secure data storage systems accessible only to authorized personnel, such as the principal investigator and their research assistants.

Phase II, the ongoing field deployment, involves similar ethical safeguards. Participants provided informed consent prior to receiving study materials, including accelerometers and study instructions. They were fully briefed on the study protocol and expectations. Participants are being compensated with a US $100 Amazon e-gift card upon verified completion of study requirements, including consistent accelerometer wear and tracking log submissions over the 8-week data collection period. Additional incentives in the form of e-gift cards are offered to top performers on the app’s gamified leaderboard to encourage engagement. All data collected during this phase continue to be anonymized and securely managed through access-controlled systems. No identifiable participant images or information will be included in future manuscripts or supplementary materials.

### PuzzleWalk mHealth System

PuzzleWalk is a gamified, behavior change theory–guided mobile app designed to promote regular PA participation among autistic adults by leveraging practical behavior change techniques and principles of self-determination theory [12,20,28]. Key innovative features include a step-to-game conversion algorithm, which translates users’ daily step counts into time for solving image-based puzzle games, highlighting iconic cityscapes from around the world. This user-centered design builds on the strengths of autistic individuals in visual learning and fosters intrinsic motivation through autonomy, relatedness, and competence. To achieve these core elements of self-determination theory, PuzzleWalk incorporates self-monitoring of step counts to support autonomous app engagement, visual puzzle games, contingent rewards to enhance competence, and a competition-based leaderboard and shared goals to foster relatedness among autistic users. PuzzleWalk v2 builds on the original version through iterative design enhancements guided by feedback from key stakeholders during the participatory workshop phase. A major advancement in PuzzleWalk v2 is the inclusion of improved accessibility features, such as step-by-step visual guides, simplified interface navigation, and animated icons and buttons to enhance user-friendliness. Another key improvement from v1 to v2 is the introduction of a gamified goal-tracking feature that uses a quest-based design, allowing users to unlock puzzle rewards by reaching step count milestones (Figure 2). The leaderboard scores are determined by combining accumulated step counts and puzzle points. Top scorers on the leaderboard are eligible to receive tangible incentives (eg, Amazon e-gift cards) at the end of each month. Importantly, the PuzzleWalk system automatically resets leaderboard scores at the end of each month to encourage consistent PA engagement among users. Detailed descriptions of the PuzzleWalk v1 system can be found in previous studies [20,28].

**Figure 2 figure2:**
[figure not shown]
Functional interfaces of PuzzleWalk v2.

### PA and SB Assessment

PA, including daily step counts, light PA, and MVPA, as well as sedentary time, will be measured using research-grade CentrePoint Insight Watches (ActiGraph). Triaxial accelerometers by ActiGraph have been widely used to provide objective assessments of PA and sedentary time, demonstrating moderate-to-high reliability across diverse clinical populations [29]. All participants will wear an accelerometer on their nondominant wrist during waking hours, except during water activities. They will be instructed to continuously wear an accelerometer for 7 consecutive days, capturing behavioral data from at least 3 weekdays and 1 weekend day across the 4 data collection intervals (ie, weeks 1, 3, 5, and 8). Compliance will be supported through regular check-ins and reminders.

Accelerometers will be programmed to collect data in 60-second epochs. Levels of activity intensity and sedentary time will be classified using activity counts per minute (CPM) cut point values: sedentary (<2860 CPM), light PA (2860-3940 CPM), and MVPA (≥3941 CPM) [30]. These cut point thresholds, established by Montoye et al [30], underwent cross-validation in both structured laboratory and free-living conditions with adults. A valid day will be defined as a minimum of 10 hours of accelerometer wear time a day. To be included in the data analysis, participants must have at least 3 valid days of accelerometer wear during each data collection period [31]. Despite the absence of a definitive consensus on the required number of valid days, previous research commonly accepts 3 days to 4 days as adequate for reliable estimation of one’s general patterns of PA engagement [32,33]. Nonwear time will be defined as 90 minutes of consecutive zero activity counts, with a 2-minute spike tolerance [34]. The accelerometers will be programmed to record PA and sedentary time at a default sampling frequency of 32 Hz. The CentrePoint cloud portal will streamline management and initial analysis of accelerometry data through a manufacturer-provided mobile app (ie, CentrePoint Connect app). Given the project’s timeline, participants will be required to install the app on their devices to remotely synchronize accelerometry data and prevent data loss before the device storage capacity (ie, 30 days or 512 MB) is reached. Processed raw accelerometry data will be securely managed and stored in the customizable CentrePoint cloud, and the research team will have a real-time overview of participant compliance (eg, at least 10 hours of accelerometer wear per day), data outcomes, and overall study progress.

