### Data Analysis

Accelerometry data will be systematically analyzed by inspecting ranges and addressing missing values in accordance with the previously outlined validation protocol. The raw accelerometry output will be transformed into CPM values and processed using ActiLife software (ActiGraph). To account for the typical lifespan of mHealth interventions (eg, ≤3 months) [35], an intention-to-treat approach will be applied to ensure external validity. Baseline comparisons between autistic adults with and without mild intellectual disability, as well as between male and female autistic adults, will be conducted using independent *t* tests and chi-square tests. We will perform repeated measures ANCOVA to examine the changes in participants’ objective levels of PA and sedentary time before, during, and after the 6-week intervention, adjusting for baseline characteristics, including age, sex, mild intellectual disability, and BMI. Bonferroni post hoc tests will be performed if a significant difference is found between time points. Dependent variables will include light PA, MVPA, sedentary time (minutes per day), MVPA in bouts of >10 minutes per day, steps per day, and user engagement (eg, number of app login sessions and time spent on app use per day). Independent variables will be each time point and intervention. Pearson correlation analyses will be used to examine the relationship between the levels of PA, sedentary time, and user engagement during the intervention period. We will perform data analyses using SPSS v29 (IBM Corp), and the significance level will be set at *P*<.05 (2-tailed).

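### The promised intention-to-treat analysis is contradicted by an inclusion rule that keeps only participants with valid accelerometry in all four periods, which makes the analysis complete-case

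*Protocol article*

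**What the plan says.** Four statements in the protocol article bear on who is analysed.

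- **Inclusion rule (PA and SB Assessment).** A valid day needs 10 hours of wear. To enter the analysis, "participants must have at least 3 valid days of accelerometer wear during each data collection period". The same section lists the periods as weeks 1, 3, 5 and 8.
- **Analysis principle (Data Analysis).** "an intention-to-treat approach will be applied to ensure external validity". The reason offered is the usual lifespan of mHealth interventions.
- **Missing data and model (Data Analysis).** Missing values are to be handled under the validity rules given earlier. The model is repeated measures ANCOVA in SPSS v29, adjusted for age, sex, mild intellectual disability and BMI. No imputation or likelihood-based method is named.
- **Sample size (Sample and Recruitment Strategies).** The target is given as follows: "we project a total sample of 55 autistic adults to achieve a power of 0.9". It rests on α = .05, f = 0.2, a correlation of 0.4 between measurements and four time points per person. No allowance for loss is stated. The Abstract plans for about 70 participants, and the Results section reports 69 enrolled by July 2025.

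**The concern.** Intention-to-treat means that enrolled people stay in the analysis whatever their compliance. A rule that removes a person for failing the wear standard in any one of four weeks does the opposite.

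Two things are at stake. The first is selection. There is no control arm, so the only contrast is each participant's change from their own baseline, and nothing offsets selective retention. The article itself supplies a possible mechanism. The Discussion expects high engagement to go with more activity and less sedentary time, and says engagement with mHealth interventions is generally short-lived. If people who lose interest also stop wearing the watch, those left at week 8 would tend to be the ones who did better. For a study of feasibility and real-world use, the people who disengage are part of the question.

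The second is precision. The 55 in the power calculation are people with all four measurements, and the rule discards good weeks along with bad ones.

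**Working it through.** **1. Reproduce the stated sample size.** Inputs from Sample and Recruitment Strategies: f = 0.2, correlation ρ = 0.4, m = 4 measurements, α = 0.05. G*Power's within-factors test with one group and sphericity uses

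λ = f² × N × m / (1 − ρ), df1 = m − 1, df2 = (N − 1)(m − 1).

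For N = 55: λ = 0.04 × 55 × 4 / 0.6 = 14.67, df = 3 and 162, power 0.903. For N = 54, power is 0.897. The smallest N for 0.90 is therefore 55, as stated.

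**2. How many exclusions the enrolment can absorb.**

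- From 70: 70 − 55 = 15, or 21.4%.
- From 69: 69 − 55 = 14, or 20.3%.

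With complete data on 69 or 70, power would be about 0.96. Under the all-periods rule, loss from 70 gives:

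| Excluded (assumed) | Remaining | Power |
|---|---|---|
| 10% | 63 | 0.941 |
| 20% | 56 | 0.909 |
| 25% | 52 | 0.884 |
| 30% | 49 | 0.863 |
| 40% | 42 | 0.798 |

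**3. From per-period validity to all-four validity.** The article gives no compliance rate, so these rates are assumptions.

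*Independent periods.* To keep 55 of 70, each period needs (55/70)^(1/4) = 94.1% valid; from 69, (55/69)^(1/4) = 94.5%.

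- 90% per period: 70 × 0.9⁴ = 45.9; power 0.828 at 45 and 0.837 at 46.
- 85% per period: 70 × 0.85⁴ = 36.5; power 0.724 at 36.

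*Validity correlated within person.* If the same people tend to fail repeatedly, fewer are lost in total. With a random-intercept logit model (assumed SD 1.5 to 2.5):

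- 90% per period: about 51 to 54 of 70 remain, power about 0.88 to 0.90.
- 85% per period: about 43 to 48 remain, power about 0.81 to 0.85.

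**4. Possible size of selection bias (illustration only).** Set the true mean change to zero. Assume a correlation of 0.2 to 0.5 between engagement and change, a correlation of 0.5 between engagement and the tendency to valid wear, and 20% to 40% excluded. Those retained then show an apparent gain of about 0.04 to 0.16 SD of change. None of these inputs comes from the article.

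**5. Can the two rules be reconciled?** The inclusion sentence takes the participant as its subject and requires every period. The Data Analysis section makes that rule the way missing values are handled and adds nothing that would bring excluded people back. The reason given for intention-to-treat does not concern who is analysed.

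**The case against.** There are two softer readings of the text. Intention-to-treat might mean only that people are analysed whatever their app use: someone who abandons the app but keeps wearing the watch stays in. Or the 3-day rule might be meant as a reliability standard for each week, since the surrounding text discusses how many days give a stable estimate. The first does not help a participant who misses one week of wear. The second does not fit the literal sentence, and standard repeated measures ANCOVA drops a case with a missing time point anyway.

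Other objections stand and limit the point.

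- A reader might infer that the results will be biased. The article has no data linking watch wear to app engagement. The US $100 payment depends on consistent wear and log submission, not on app use, and there are reminders, check-ins and real-time compliance monitoring. These may weaken the link between losing interest and not wearing the watch.
- A reader might infer that the study is underpowered or that 55 is wrong. It is not wrong, and 69 to 70 enrolled leaves a margin of 20% to 21%.
- The independence figures are the pessimistic end. Persistent disengagement, which the bias argument presupposes, means correlated validity and fewer people lost.
- This is a single-arm pilot with a controlled trial to follow, and detailed missing-data methods are often left to an analysis plan. But the article itself fixes the inclusion rule, the principle, the missing-data rule and the model, and these conflict.

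**Conclusion.** The contradiction holds on the text: the analysis as specified is complete-case and cannot be called intention-to-treat. This rests on no numerical assumption.

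The consequences are conditional. Overstated benefit is a risk that follows from the article's own expectations about engagement; its direction is plausible and its size unknown. Power drops below 0.90 only if exclusions exceed 14 of 69 or 15 of 70. Taking independent and strongly correlated periods as the two ends, an assumed 90% valid per period leaves about 46 to 54 of 70 (power about 0.83 to 0.90), and 85% leaves about 36 to 48 (power about 0.72 to 0.85).

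**What to change.** 1. Apply the 3-day rule to the period, not the participant: a week with fewer valid days is set to missing and the person's other weeks are kept.
2. Analyse every enrolled participant with at least one valid period in a linear mixed model (SPSS MIXED, REML, time as a categorical factor, the same covariates).
3. Keep the four-period complete-case analysis as a sensitivity analysis.
4. State that power 0.90 refers to 55 participants with all four periods, and give the loss assumed behind the target of about 70.

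This costs a change of wording in the analysis plan. SPSS v29 fits the model and no new data are needed. The downside is that the mixed model assumes data missing at random. It recovers the discarded data and reduces bias from selective non-wear, but may not remove it if non-wear depends on unobserved change.

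If the complete-case rule is kept instead, drop the intention-to-treat label and limit the conclusions to participants who complied with wear in all four periods.
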